**Discussion:**

Comprehensive assessment of symptoms and neurophysiological biomarkers will contribute to understanding the differential efficacy of the tested treatment protocols, identifying biomarkers for treatment response, and shedding light into underlying mechanisms of TBS. Our findings will inform future clinical trials and aid in personalizing treatment selection and scheduling for individuals with MDD.

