### Study objectives

No large-scale study has compared left unilateral versus bilateral sequential TBS for treating symptoms of MDD. The primary aim of this naturalistic, randomized double-blinded non-inferiority trial is to investigate the efficacy of unilateral (i.e., iTBS to the left DLPFC) and bilateral sequential (i.e., cTBS to the right DLPFC combined with iTBS to the left DLPFC) on reducing clinical symptoms of MDD. Based on previous research, we hypothesize that both treatments will effectively decrease depressive symptoms to a comparable degree (i.e., non-inferior) [33, 34, 61]. The incorporation of covariates during analysis may reveal a superiority of bilateral sequential TBS over unilateral treatment in specific subgroups. These subgroups include older individuals (≥ 60 years-old; [62], and/or individuals presenting with comorbid anxiety, and post-traumatic stress disorder [33, 63]). As mentioned, the clinical efficacy of rTMS is time limited [57, 58]. Therefore, this study will also investigate the efficacy of a six-month flexible maintenance phase. Additionally, to better understand the TBS-induced neurophysiological changes and their associations with therapeutic responses, multiple objectively measured neurophysiological variables will be assessed in this study. See Table 1 for a brief description of outcome measures and detailed hypotheses of this study. Ultimately, this study aims to: 1) inform whether unilateral TBS performed over the DLPFC is non-inferior to bilateral sequential TBS on treating MDD, 2) provide insight on neurophysiological mechanisms associated with treatment-induced effects and their longitudinal changes resulting from treatment, thus providing biomarkers of treatment response, and 3) explore neurophysiological markers, demographics, and clinical characteristics that may help identify responders and non-responders to treatment, paving the way for a more refined and personalized approach to TBS treatment.

**Table 1 Tab1:** Outcomes and hypotheses of the study

Outcome	Rationale	Hypothesis
Clinical (primary)	Investigate changes in severity of depressive symptoms	Unilateral TBS will be non-inferior in comparison to bilateral sequential TBS on reducing depressive symptoms

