## Methods

### Study design and overview

This is a double-blinded randomized, naturalistic, non-inferiority trial comparing unilateral vs bilateral sequential TBS (iTBS in the left vs cTBS in the right followed by iTBS in the left DLPFC, respectively). Participants enrolling in this study are referred by their physician to receive rTMS for the treatment of MDD and are randomized in a 1:1 ratio to receive either unilateral or bilateral sequential TBS. The study design and timeline of assessments and treatment schedule is presented in detail in Fig. 2.

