## Data analysis

All statistical tests will be two-tailed, and significance (*p*-value) will be set at α = 0.05. All analyses will be performed on SPSS (Chicago, US) and/or using the open-source R statistical software (R core Team, Vienna, Austria and the R-Studio package rstatix; Kassambara, 2022). All data will be reported descriptively to summarize population characteristics. Unless otherwise stated, continuous data will be reported as mean and standard deviation (mean ± SD) and dichotomous variables will be reported as frequency (i.e., percentage) values.

All participants will be included in the analyses ‘as-randomized’ (i.e., bilateral and unilateral TBS) and data will be analyzed regardless treatment adherence and drop-outs. To this end, missing values in the data set (due to participants missing appointments, drop-out/discharge), if present, will be appropriately managed during analysis as per previous suggested procedures for clinical research [103, 104].

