### Sample size

Based on our power calculations and the findings from exemplary studies, our sample size offers sufficient statistical power for the planned statistical tests. For example, Plewnia et al. (2014), in *n* = 32 (16/group), found clinically meaningful differences in response to treatment rate (≥ 50% reduction in baseline MADRS score) when comparing 6 weeks of bilateral sequential vs sham TBS (56% vs 25%, respectively) [42]. In *n* = 60 (15/group), Li et al. (2014) showed that 2 weeks of bilateral sequential TBS had superior effectiveness in treating depressive symptoms (≥ 50% reduction in baseline HRSD-17 score) when compared to unilateral (iTBS or cTBS) or sham TBS [106]. For our primary (non-inferiority) statistical analysis (i.e., analysis of covariance, ANCOVA), a total sample size of *n* = 158 was calculated [Gpower Software V.3.1 [107]; power 0.80, α = 0.05, expected effect size *Cohen’s f* = 0.25 (medium; Cohen, 1988)]. For our analysis of predictors of response (i.e., regression analysis), a total sample size of *n* = 30–39 will be required for a regression model that includes 3–6 independent (and/or controlling) variables predicting 30% (R^2^) of variance in the outcome (dependent) variable (Gpower Software V.3.1 [107]; power 0.80, α = 0.05, expected effect size *Cohen’s f*^*2*^ = 0.43) [108]. All other statistical tests are exploratory and, therefore, no sample size calculations were performed. Therefore, in order to achieve the calculated sample size (*n* = 158), we aim to recruit a minimum of 171 individuals, considering an anticipated dropout rate of 6–8% based on previous research [37]. Our recruitment efforts will be capped at a maximum of 256 participants, aligning with our capacity to provide TBS treatment over a five-year timeframe.

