### Predictors of treatment response

Exploratory relationships across outcome measures will be investigated using Pearson’s or Spearman’s correlation coefficients for normal and non-normal distributed data, respectively. Specifically, relationships between baseline levels of neurotransmitters, cortical excitability, and capacity of plasticity (rsfMRI and MRS, TMS, and TMS-EEG, respectively) and the degree of change (∆ pre-post treatment) in the assessed clinical outcomes will be performed to identify potential neurobiological predictors of response to treatment. As well, to provide some insight on possible neurobiological mechanisms involved in response to treatment, correlation analyses will be conducted between the degree of change (∆ pre-post treatment) in cortical plasticity (TMS-EEG) and clinical treatment response (e.g., HRSD-17). Additionally, regression analyses will be performed to predict response to treatment (e.g., “responders” and “non-responders”, and HRSD-17) with the neurobiological outcomes (MRI, TMS, TMS-EEG) entered as predicting variables. We will include demographics (e.g., age, sex, levels of education, amount of benzodiazepines being taken, employment status (measure of functionality), baseline HRSD-17 (MDD symptom severity), baseline BAI anxiety, degree of resistance to pharmacotherapy, etc.) as controlling variables. To investigate predictors within each treatment group, the correlations and regression analyses will be performed separately for each group and/or with groups entered as predicting variables. A Receiver Operating Characteristic (ROC) curve analysis will be performed to investigate the ability of significant predictors to classify response to treatment (achieved remission, "yes" or "no", based on ≥ 50% reduction from baseline HRSD-17 score; dependent variable). The area under the ROC curve with 95% CI will be investigated and the ‘cut-off point’ best classifying remission and its respective sensitivity and specificity percentage values will be identified.

Biological sex will be considered during analyses. Biological sex (male, female) will be inputted as predicting outcome variables (dependent) during regression analysis predicting the independent variables. As well, differences in treatment response and neurophysiological measures between the two biological sexes will be explored using independent t-tests.

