### Brain biomarkers – assessing CNS effects and predicting treatment response

In clinical research, efforts have been recently made to improve upon the practice of delivering treatments in a ‘*one size fits all*’ perspective [44]. This is the reason why exploring cross-modal biomarkers (e.g., clinical characteristics/neuroimaging/neurophysiology) is highly encouraged in clinical trials as they would help to identify participants who would and would not benefit from treatment, and provide insight on the underlying cause behind the different responses [44, 112, 113]. We expect that not every participant will respond clinically to the TBS treatments [114, 115], therefore investigating biomarkers is an important aspect of this study. The multiple neurophysiological and neuroimaging experiments collected will help us to identify predictors of response that could serve to guide participant selection for TBS treatment, and guide future non-invasive brain stimulation research on the development of novel protocols for participants profiled as non-responders.

Biomarkers indexing effectiveness of non-invasive brain stimulation protocols traditionally rely on investigation of corticospinal excitability assessed by TMS-evoked MEPs. Analysis of its EMG features provide indexes of excitatory and inhibitory receptor activity involved in LTP and LTD [116, 117], processes of strengthening and weakening synaptic connections, respectively, in which neuroplasticity relies [118]. Several studies have shown that, although probed in the motor cortex (M1), MEPs are associated with functionality and symptoms inside and outside motor regions, such as cognition, migraines, sleep deprivation, cognitive impairment, pain, and others [117, 119–124]. For this reason, assessment of MEPs is largely used in research attempting to understand CNS-induced changes resulting from various interventions and, especially, to provide biomarkers of disease, symptom progression, and recovery in the lesion-disrupted brain (e.g., stroke, Multiple Sclerosis, Alzheimer’s, Parkinson’s, mild cognitive impairment, and others [116, 117, 125–127]).

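### The predictor analyses name no marker-by-arm interaction, and both arms receive active TBS, so they cannot support the treatment-selection claims made for them

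*Protocol article*

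**What the plan says.** **Analysis.** Under Predictors of treatment response, baseline MRS, resting-state fMRI, TMS and TMS-EEG measures are correlated with pre-post clinical change and entered in regressions for response. For predictors within each treatment group, "the correlations and regression analyses will be performed separately for each group and/or with groups entered as predicting variables". Significant predictors then go into ROC analysis to find cut-offs. The correlations are called exploratory. The only interaction named in the analysis sections is Time × Group, under Effectiveness of TBS treatment, and it contains no marker.

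**Design.** Participants "are randomized in a 1:1 ratio to receive either unilateral or bilateral sequential TBS". The section on unilateral and bilateral treatment gives both arms active left iTBS; only the right-sided cTBS is active or sham. The Abstract describes the unilateral arm differently (active right cTBS, sham left) and the two passages must be reconciled, but the arm is active in either account. No arm goes without active TBS.

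**Claims.** The abstract's Discussion says the findings will "aid in personalizing treatment selection and scheduling for individuals with MDD". The opening of the main Discussion goes furthest: it says the findings will identify response biomarkers, crucial above all for selecting clinic patients for TBS. Clinical implications repeats the treatment-selection aim. Study objectives is more cautious about the third aim, "paving the way for a more refined and personalized approach to TBS treatment".

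**The concern.** Two selection questions are mixed together.

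1. **Who should be offered TBS?** This needs the marker's relation to the difference between TBS and no TBS. With active TBS in both arms, a marker that tracks HRSD-17 change may only identify patients who would improve anyway, through natural course or expectation. No analysis of these data can separate the two.
2. **Unilateral or bilateral?** Randomisation does allow this to be answered, but only by comparing the marker's slope between arms. A group main effect shifts the mean outcome and leaves the slope common. Separate per-arm tests do not compare the slopes: significance in one arm and not in the other is weak evidence of a difference.

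At stake is that a marker equally prognostic in both arms could be read as a reason to prefer one arm, or a prognostic marker read as grounds to offer or withhold TBS.

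**Working it through.** **Inputs from the article.** Two-sided α = 0.05 (Data analysis: "All statistical tests will be two-tailed, and significance"); 1:1 allocation; 158 evaluable participants, i.e. 158/2 = 79 per arm; cap of 256, i.e. 128 per arm (Sample size, Participants). The regression calculation assumes 3–6 "independent (and/or controlling) variables predicting 30"% of variance, with "power 0.80, α = 0.05, expected effect size" f² = 0.43, and gives n = 30–39.

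**The plan's own figure.** f² = R²/(1−R²) = 0.30/0.70 = 0.43. The overall F test (noncentrality f²·N, degrees of freedom k and N−k−1) first reaches 80% power at N = 30, 33, 36 and 39 for k = 3, 4, 5 and 6. The stated range reproduces exactly. It sizes a test of R² = 0, not of a difference between arms.

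**Assumption.** The article gives no correlation for a single marker, so r is varied from 0.20 to 0.40.

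**Chance of significance in exactly one arm when the true correlation is the same in both.** Power within one arm, by Fisher's z, is p = Φ(atanh(r)·√(n−3) − 1.96). The arms are independent, so the chance that exactly one is significant is 2p(1−p). Example for n = 79, r = 0.25: atanh(0.25) = 0.2554; 0.2554 × √76 = 2.227; p = Φ(0.267) = 0.605; 2 × 0.605 × 0.395 = 0.478.

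| r (both arms) | p, 79/arm | exactly one | p, 128/arm | exactly one |
|---|---|---|---|---|
| 0.20 | 0.424 | 49% | 0.620 | 47% |
| 0.25 | 0.605 | 48% | 0.815 | 30% |
| 0.30 | 0.770 | 35% | 0.933 | 12% |
| 0.35 | 0.890 | 20% | 0.983 | 3% |
| 0.40 | 0.958 | 8% | 0.997 | 0.5% |

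For a null marker (r = 0) the figure is 2 × 0.05 × 0.95 = 9.5% at any n.

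**Simulation check at r = 0.25 (10,000 trials).** Exactly one arm is significant in 47% of trials at 79 per arm and 30% at 128. A test of the slope difference is falsely positive in 5.0% and 4.9%. Pooled over arms, the same marker is significant in 89% and 98% of trials, although it carries no information on which arm to choose.

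**Power of the interaction test.** Using Φ((atanh(r₁) − atanh(r₂))/√(2/(n−3)) − 1.96), with assumed r = 0.3 in one arm and 0 in the other: 0.3095/√(2/76) = 1.908, power 48% at 79 per arm; 0.3095/√(2/125) = 2.447, power 69% at 128. For 80% power, n = 2 × (2.80/0.3095)² + 3, about 167 per arm, above the cap of 128.

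**The case against.** **No passage says that one-arm significance will decide the choice of arm.** A reader might infer that chance differences between arms will be reported as treatment selectors. The text does not support that: the stated purpose is to look at predictors within each group, the correlations are labelled exploratory, and the biomarker hypotheses in Table 1 name no difference between arms. This stands, and it limits the point to what could be misread.

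**The group-as-predictor option may include an interaction in a fuller plan.** The text does not exclude one. But it does state a method, and neither named option tests slope differences, so naming the term improves a stated method and does not ask for omitted detail.

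**Some of the language is general or hedged.** The phrase "identify participants who would and would not benefit from treatment" explains why biomarker research is encouraged in clinical trials; it is not a promise of this trial. Study objectives and the sentence on this study under Brain biomarkers are cautious too. That stands. The claim at the opening of the Discussion is not hedged.

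**The size depends on r.** The risk is large for weak to moderate correlations and small from about 0.40. For the whole regression model as sized (R² = 0.30), power within one arm of 79 exceeds 99%, so discordance is about 1% or less. Single markers within such a model could be much weaker.

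**The 25% sham response cited under Sample size** is 4 of 16 patients on another scale (exact 95% interval about 7–52%). It does not show that any marker predicts improvement without TBS, and nothing here rests on it.

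**Two active arms are a deliberate choice** for a non-inferiority trial. Agreed: this half of the point concerns wording only.

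**Conclusion.** The point holds in a limited form. As both arms receive active TBS, associations between markers and outcome are prognostic under TBS; the statement at the opening of the Discussion about selecting patients for TBS goes beyond what the design can show. The unilateral-versus-bilateral question can be answered, but not by per-arm results or a group main effect. For assumed equal correlations of 0.20 to 0.30, the chance of significance in exactly one arm is 35–49% at 79 per arm and 12–47% at 128, against 5% for an interaction test. It falls to 8% and under 1% at r = 0.40. These correlations are assumptions. The error is one that the stated analysis invites, not one that the article says will be made.

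**What to change.** - **Predictors of treatment response:** for each marker, fit outcome on baseline HRSD-17, arm, marker and marker × arm. Base any biomarker statement about unilateral versus bilateral TBS on the interaction estimate and its confidence interval, labelled exploratory because there are many markers (with 20 independent null markers, 1 − 0.95²⁰ = 64% chance of at least one p < 0.05). Keep within-arm correlations as description.
- **Opening of the Discussion** first, then the abstract's Discussion, Brain biomarkers and Clinical implications where they refer to this trial: describe pooled associations as prognostic of outcome under TBS, not as showing who benefits from TBS.

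**Cost:** one model term and some rewording; no new data and no change to conduct. The interaction estimates will be imprecise at the planned sizes, so fewer selection claims can be made.

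### ROC accuracy and cut-offs are planned on markers already selected for significance, with no other data source named, so the apparent AUC, sensitivity and specificity are biased upward.

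*Protocol article*

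**What the plan says.** All of this is in the protocol article. Under Predictors of treatment response, baseline resting-state fMRI, MRS, TMS and TMS-EEG measures are correlated with clinical change and entered in regressions for response. On splitting by arm, "the correlations and regression analyses will be performed separately for each group and/or with groups entered as predicting variables". The general rule under Data analysis is: "All statistical tests will be two-tailed, and significance (*p*-value) will be set at α = 0.05". No multiplicity control is stated for the predictor step; the Bonferroni adjustment under Effectiveness of TBS treatment covers pairwise comparisons in the mixed models.

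The ROC analysis follows, its purpose being "to investigate the ability of significant predictors to classify response to treatment". One output is the AUC with its confidence interval. The other is a threshold chosen from the data: "the ‘cut-off point’ best classifying remission and its respective sensitivity and specificity percentage values will be identified".

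On status, Sample size makes every test other than the ANCOVA and the predictor regression exploratory. On use, the third aim under Study objectives is to explore markers that may help identify responders. The opening paragraph of the Discussion goes further and gives participant selection for TBS in clinical settings as the most important use of the biomarkers.

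**The concern.** The text fixes an order: significance decides which markers reach the ROC curve, the curve is drawn, and the cut-off is then optimised on it. No second cohort, split sample or resampling step is named, so all three stages fall on the same patients.

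A marker that passes a 5% test in a sample must already separate responders from non-responders in that sample, whether or not it does so in the population. Its AUC there cannot be near 0.50, and a CI computed as if the marker had been chosen in advance does not show this. Choosing the best cut-off on the same curve adds optimism to sensitivity and specificity.

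At stake is whether a published AUC and cut-off can be taken at face value by someone deciding which patients to treat. The unilateral versus bilateral comparison is not at stake.

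**Working it through.** **Inputs from the protocol article**
- Screening level: 0.05 two-sided (Data analysis).
- Sizes: 158 analysed, so 158/2 = 79 per arm (Sample size); maximum 256 (Participants).
- Candidates: six TEP windows over two sites = 12; delta-to-gamma ERSP bands over two sites, about 5 × 2 = 10 (the band count is an assumption); MEP, SICI, LICI and ICF = 4; three ACC regions for one seed = 3; GABA and Glx = 2. Sum: 12 + 10 + 4 + 3 + 2 = 31, so roughly 30.
- Outcome: at least 50% reduction in HRSD-17. The ROC sentence calls this remission, whereas Primary outcome measure defines remission as HRSD-17 ≤ 7; I used the 50% rule.

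**Assumptions:** 45% response (the article states no rate for this trial), independent markers, no marker carrying information.

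**Step 1. Chance of at least one false significant marker:** 1 − 0.95^m.
- m = 10: 1 − 0.95^10 = 0.40
- m = 25: 0.72
- m = 30: 0.79
- m = 40: 0.87

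If the markers share a correlation of 0.5 (assumed), the figure for m = 40 falls to about 0.58–0.60.

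**Step 2. The AUC a marker needs just to be selected.** For a t-test on responder status the critical standardised difference is d = t × √(1/n1 + 1/n0). For normal markers AUC = Φ(d/√2).
- n = 79 (36 v 43): d = 1.991 × 0.2259 = 0.450; AUC = Φ(0.318) = 0.62
- n = 158 (71 v 87): d = 1.975 × 0.1599 = 0.316; AUC = Φ(0.223) = 0.59
- n = 256 (115 v 141): d = 1.969 × 0.1256 = 0.247; AUC = Φ(0.175) = 0.57

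Apart from the small difference between the t-test and the rank-based AUC, a noise marker selected this way cannot show less than these values.

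**Step 3. Mean apparent AUC of a selected noise marker (simulation, truth 0.50)**

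| n | Selected on responder status | Selected on continuous HRSD-17 change |
|---|---|---|
| 79 | 0.65 | 0.62 |
| 158 | 0.61 | 0.58 |
| 256 | 0.58 | 0.57 |

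Both columns matter because the article's correlations use continuous change, while its regressions also allow responder status.

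**Step 4. CI and cut-off** (50% response assumed). Given a selection, the conventional 95% CI of the best noise marker excludes 0.5 in about 85–97% of cases when selection uses responder status, and in 57–59% when it uses continuous change. At n = 158 with 25 candidates and selection on responder status, the best (Youden) cut-off shows sensitivity 0.60 and specificity 0.62; in new patients these are 0.49 and 0.51.

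**Step 5. Does resampling repair it?** 25 candidates, 50% response, model built from all selected markers, selection repeated inside 5-fold cross-validation:

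| Setting | Apparent | Cross-validated | New patients |
|---|---|---|---|
| Noise, n = 79 | 0.69 | 0.53 | 0.50 |
| Noise, n = 158 | 0.635 | 0.52 | 0.50 |
| Noise, n = 256 | 0.60 | 0.51 | 0.50 |
| One real marker (d = 0.5) plus 24 noise, n = 158 | 0.68 | 0.60 | 0.60 |

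The correction removes nearly all the bias and keeps the real signal.

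**The case against.** The strongest reply is that this is a condensed article. It does not say that the AUC will go uncorrected, and a full protocol or analysis plan could add internal validation. That the same patients are used throughout is an inference from the absence of any other data source. This stands as a limit. It does not remove the point, because the article itself prescribes selection by significance followed by ROC and cut-off, and that sequence is biased if followed as written.

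The second reply is that the analysis is exploratory. That is right, and it limits the severity. It does not settle the matter, because the Discussion gives the biomarkers a clinical use.

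The third is that the size depends on assumptions. This also stands in part. Table 1 states only a few predictor hypotheses, the candidate count is mine, and correlated markers make a false selection less likely. The bias once a marker is selected hardly changes.

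Three stronger readings are tempting, and the documents do not support them:
- A reader might quote a null AUC of about 0.71. That needs 40 noise markers, a single arm of 79 and all selected markers combined in one classifier, which the article does not describe. It is a worst case.
- A reader might conclude that the predictor regression is too small, because "a total sample size of *n* = 30–39 will be required for a regression model that includes 3–6 independent (and/or controlling) variables" while the text lists eight control variables and an open-ended remainder. The stated 30 and 39 reproduce for 3 and 6 variables at f² = 0.43. Twelve variables would need 52 and twenty 67, both below 79 per arm, so no shortfall is shown.
- A reader might fault the per-arm screens and ask for marker-by-arm terms instead. The article already allows group as a predictor, so this is a preference and not an error.

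**Conclusion.** The concern holds for the sequence as written. The apparent AUC, sensitivity and specificity will be too high, and the ordinary CI does not reflect the selection. For a noise marker the mean excess over 0.50 is about 0.12–0.15 in one arm of 79, 0.08–0.11 at n = 158 and 0.07–0.08 at n = 256. It is therefore modest in the pooled sample and larger per arm. About 40–80% of datasets would offer at least one such marker with 10 to 30 independent candidates, and fewer if the markers are correlated.

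These figures rest on the assumed 45% response rate, the assumed candidate count, independence, and no true signal. It would be too strong to say that no published cut-off could replicate: with one real marker at n = 158 the accuracy is overstated (0.68 against 0.60) but not absent. The finding is moderate: worth correcting because of the intended clinical use, with no bearing on the primary analysis.

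**What to change.** State that the whole procedure (marker selection, model fit and cut-off choice) will be repeated inside each bootstrap resample or cross-validation fold, and that optimism-corrected AUC, sensitivity and specificity will be reported. Correcting only the final ROC step, with the selected markers held fixed, would leave the selection bias in place. Label any uncorrected values as apparent and hypothesis-generating. Name the ROC outcome consistently as response or remission, so that the cut-off refers to one definition.

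The cost is some extra computing in R, which the plan already allows. The reported AUCs will be lower and their CIs wider. No additional patients or measurements are needed.
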